## Abstract

**Background:**

Angiotensin-converting enzyme inhibitors and the angiotensin-receptor blocker valsartan ameliorate ventricular remodeling after myocardial infarction (MI). Based on previous clinical trials, a maximum clinical dose is recommended in practical guidelines. Yet, has not been clearly demonstrated whether the recommended dose is more efficacious compared to the lower dose that is commonly used in clinical practice.

**Method/Design:**

Valsartan in post-MI remodeling (VALID) is a randomized, open-label, single-blinded multicenter study designed to compare the efficacy of different clinical dose of valsartan on the post-MI ventricular remodeling. This study also aims to assess neurohormone change and clinical parameters of patients during the post-infarct period. A total of 1116 patients with left ventricular dysfunction following the first episode of acute ST-elevation MI are to be enrolled and randomized to a maximal tolerable dose (up to 320 mg/day) or usual dose (80 mg/day) of valsartan for 12 months in 2:1 ratio. Echocardiographic analysis for quantifying post-MI ventricular remodeling is to be conducted in central core laboratory. Clinical assessment and laboratory test are performed at fixed times.

**Discussion:**

VALID is a multicenter collaborative study to evaluate the impact of dose of valsartan on the post-MI ventricular remodeling. The results of the study provide information about optimal dosing of the drug in the management of patients after MI. The results will be available by 2012.

**Trial registration:**

NCT01340326

## Background

Progressive enlargement of the heart chamber and deterioration of contractile function after myocardial infarction (MI), termed post-MI ventricular remodeling, is associated with development of heart failure and poor prognosis [1-3]. The magnitude of post-MI remodeling is influenced by several determinants, most notably infarct size [4], but also by ventricular wall stress [5], patency of infarct-related artery [6], and a number of neurohormonal factors [7]. Thus, the consequence of post-MI remodeling varies among patients with acute MI even in the era of reperfusion therapy [8]. Modification of neurohormonal acitivities, particularly the rennin-angiotensin-aldosterone system (RAAS), can significantly influence the process of ventricular remodeling after acute MI. Suppression of angiotensin activity either by inhibition of angiotensin-converting enzyme (ACE) [9-11] or by blockade of angiotensin II receptor [12] attenuates ventricular dilatation and improves clinical outcomes. Based on the results from major pivotal clinical trials, it is usually recommended in practical guidelines that the maximal clinical dose of ACE inhibitors used in those trials be given to patients after acute MI [13,14]. A seminal finding that the neurohormone level is linearly related with mortality [15] in patients with heart failure also suggests the potential benefit of higher doses.

However, the optimal level of RAAS antagonism in the treatment of heart failure or post-MI remodeling is still a matter of debate. Although administration of higher dose of angiotensin-converting enzyme (ACE) inhibitor was more beneficial than lower dose in animal model of post-MI remodeling [16], results of clinical studies were not confirmatory. In the VALIANT study [17], addition of ARB valsartan to ACE inhibitor resulted in similar degree of post-MI left ventricular (LV) remodeling compared to either drug alone, although in the Val-HeFT study [18], LV remodeling in heart failure was more favorable in the combination therapy group. In several clinical studies that directly compared different doses of ACE inhibitors in patients with chronic heart failure, the results of clinical outcomes as well as neurohormonal responses were inconsistent, and sometimes irrelevant because of the impractical dosing of drugs chosen for the comparison. In the ATLAS study [19], patients receiving high-dose lisinopril (32.5-35.0 mg/day) had a nonsignificant (8%) lower risk of death and a significant (12%) lower rate of death and hospitalization compared with patients receiving low-dose lisinopril (2.5-5.0 mg/day). The CHIPS trial [20] compared low-dose (50 mg/day) with high-dose (100 mg/day) captopril therapy and demonstrated a nonsignificant trend toward less worsening heart failure and hospitalization in the high-dose group. In the NETWORK trial [21], there was no difference in the primary endpoint of combined death, heart failure-related hospitalization, and worsening of heart failure among the three groups of low dose (5 mg/day), medium dose (10 mg/day), and high dose (20 mg/day) enalapril therapy. Furthermore, the lower dose used in NETWORK (enalapril 5 mg/day) [21] was too small, and the higher dose used in ATLAS (lisinopril 35 mg/day) [19] was excessive for practical use. The recent publication of the Heart failure Endpoint evaluation of Angiotensin Antagonist Losartan trial (HEAAL) presented notable evidence of the superiority of 150 mg/day of losartan versus 50 mg per day on the primary outcomes of death or hospitalization in patients with systolic heart failure [22]. However, the study subjects were limited to patients who were intolerant to ACE inhibitors [22], precluding extrapolation of the result to general patients. Furthermore, the optimal dosing of ARB agents has not been explored in the population of post-MI. Thus, the question of whether submaximal dose of ARB, which are lower than those in major pivotal trials but typically used in clinical practice, can offer similar benefit in post-MI ventricular remodeling remains to be solved. This is more so in the Asian population, wherein moderate dose ARB has been shown to provide sufficient protection from cardiovascular risk [23]. Therefore, the primary objective of the VALsartan in post-mI remoDeling (VALID) study is to address this issue in Korean patients who suffered their first acute ST-elevation MI by comparing the impact of different doses of valsartan, an ARB demonstrated as effective as ACE inhibitor in post-MI patients [12], on echocardiographic variables of left ventricular remodeling during the follow-up period of 1 year. The comparison dose of valsartan will be 80 mg per day, as commonly prescribed after MI in Korea, versus 320 mg per day, a targeted dose in major clinical trials [12,24].

## Trial objectives

The primary hypothesis to be tested is whether high dose valsartan significantly reduces ventricular remodeling as measured by echocardiography in post-MI patients during a 12-month follow-up period, compared with the usual dose of control group.

## Methods and Design

### Study design

VALID is a prospective, multicenter, randomized, open-label, active controlled study with two parallel study groups. VALID is being conducted in 18 tertiary hospitals throughout South Korea. Participants are randomly allocated into the usual dose group and high dose group and followed-up for 12 months after discharge. Overall study algorithm is depicted in Figure 1. Baseline echocardiographic examination and neurohormonal assay are performed before discharge. Study approval was given by the institutional review board at each participating center, and consecutive, eligible patients are provided written informed consent.

**Figure 1 F1:**
[figure not shown]
**Overall study algorithm of the VALID study**. This figure illustrates the study algorithm. A total of 1116 patients will be randomly allocated into the usual dose group (n = 372) and high dose group (n = 744) and followed-up for 12 months after discharge.

### Randomization

Randomization will take place following initial echocardiographic estimation of left ventricular ejection fraction, which is conducted after stabilization by reperfusion therapy or conservative treatment. Eligible patients are randomly assigned in a 1:2 ratio to receive the usual dose (valsartan 80 mg/day) or a high dose (valsartan up to 320 mg/day). Random allocation with stratified technique is generated automatically by a centralized web based tool (http://www.cnrres.co.kr/valid) so it cannot be influenced by researchers.

### Approval

This study follows the Helsinki Declaration's principles, meaning that all patients sign a written informed consent stating that participation is voluntary and that participation can

be withdrawn at any time, without any negative consequences concerning their current or future medical treatment. This study protocol was approved by the institutional review board of Dong-A University hospital and each participating center.

### Patient population

Men and women aged 18 years or older who suffer their first acute ST-elevation myocardial infarction with the sign of LV dysfunction are eligible for this study (Table 1). In the present study, LV dysfunction is defined as an ejection fraction < 50% using a modified Simpson's rule [25]. Enrollment criteria are intended to include patients in acute stage of infarction, within 10 days of symptom onset, who are typically treated under modern therapeutic strategy. Patients are recruited regardless of whether they received reperfusion therapy, either thrombolysis or primary percutaneous coronary intervention, or not. Pharmacological therapy other than study drug, including beta-adrenergic blockers, is allowed according to the discretion of attending physician. Patients who have contraindication to the study drug or major concomitant disease are excluded (Table 1).

**Table 1 T1:** Eligibility criteria

Inclusion criteria	Exclusion criteria
Subjects > 18 years of age	Contraindication for use of ARB

Either gender	Urgent need for revascularization procedure

First episode of acute MI	Severe heart failure (NYHA IV or need for inotropic support)

Typical pain lasting ≥ 20 minutes	Persistent (>1 hour) severe hypotension (systolic blood pressure < 90 mmHg)

ST elevation of more than 1 mm in at least 2 separate leads on the ECG	Refractory or potentially lethal arrhythmias

An echocardiographic LV EF < 50%	Hemodynamically significant right ventricular infarction

Optimal recording of echocardiographic imaging of apical chamber views	Congenital heart disease

Patients who provide written informed consent	Primary valvular disease, severer than mild degree

	Idiopathic hypertrophic cardiomyopathy

	Concomitant inflammatory cardiomyopathy

	Significant renal dysfunction (serum creatinine 2.5 mg/dl)

	Significant hepatic dysfunction (serum transaminase more than 3 times normal)

	Anemia (hemoglobin < 10 mg/mL or 6 mmol/L)

	Psychiatric disorders, alcohol or drug abuse

	Life expectancy is less than 1 year

	Participation in any other pharmacological study within 2 months

	Refusal or inability to provide informal consent

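### The anaemia exclusion in Table 1 pairs 10 mg/mL with 6 mmol/L, which differ about tenfold; the mass figure should almost certainly read 10 g/dL

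*Protocol article*

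**What the plan says.** In the protocol article, Methods and Design, the Patient population section refers the reader to Table 1 for the exclusions. The haemoglobin row of that table reads "Anemia (hemoglobin < 10 mg/mL or 6 mmol/L". It is the only statement of a haemoglobin threshold in the article, and no other section repeats or corrects it. The Randomization section says that eligible patients are allocated by a central web-based tool. The Study design section puts the number of participating hospitals at 18.

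**The concern.** A threshold given in two units should describe the same concentration in both. Here the mass figure is implausibly low for an anaemia criterion, while the molar figure looks ordinary, which suggests a unit slip. This is an operative eligibility limit, so it should be usable as printed. A reader who works in mass units has no valid number in the row: taken literally, the mass limit would exclude essentially nobody.

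**Working it through.** **Inputs**

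- Mass limit: 10 mg/mL (Table 1).
- Molar limit: 6 mmol/L (Table 1).
- Molar mass of haemoglobin: not in the article. Assumed 16.114 g/mmol (monomer, per haem), with 16.0 to 16.25 as a range.

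**Does the printed pair agree?**

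- Mass limit in g/dL, no assumption needed: 10 mg/mL × 100 mL/dL ÷ 1000 mg/g = 1.0 g/dL, which is 10 g/L.
- Mass limit in mmol/L: 10 g/L ÷ 16.114 g/mmol = 0.62 mmol/L (0.615 to 0.625 over the range). The table prints 6.
- Molar limit in g/dL: 6 mmol/L × 16.114 g/mmol ÷ 10 = 9.67 g/dL (9.60 to 9.75).
- Ratio of the two limits: 9.67 ÷ 1.0 = 9.7 (9.6 to 9.75).

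The pair is not reproduced.

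**Could another molar convention rescue it?**

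With the tetramer mass (assumed 64.458 g/mmol), 6 mmol/L becomes 6 × 64.458 ÷ 10 = 38.7 g/dL, which is physiologically impossible, and 10 mg/mL becomes 10 ÷ 64.458 = 0.16 mmol/L. The mismatch gets worse.

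**Which figure is wrong?**

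| Reading of the mass limit | g/dL | mmol/L (monomer) | Agrees with 6 mmol/L? |
|---|---|---|---|
| 10 mg/mL, as printed | 1.0 | 0.62 | No |
| 10 g/dL | 10.0 | 100 ÷ 16.114 = 6.2 (6.15 to 6.25) | Yes, after rounding |

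A value of 9.67 g/dL is a plausible anaemia cut-off; 1.0 g/dL is not compatible with life. The error therefore lies in the mass figure.

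**What remains after the unit is corrected?**

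10.0 − 9.67 = 0.33 g/dL, which comes from rounding 6.2 to 6. Printing 6.2 mmol/L closes the gap: 6.2 × 16.114 ÷ 10 = 9.99 g/dL.

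**The case against.** The case against accepts the error and disputes its weight. There are four parts to it.

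- **The row largely corrects itself.** Both values stand on one line, the molar value is sensible, and no clinician would apply 1.0 g/dL. Even a literal reader who takes the two limits as alternatives still excludes everyone below 6 mmol/L. This stands, and it is why the point is minor.
- **Nothing downstream depends on it.** Haemoglobin is not an outcome, a sample-size input or a named covariate, and eligibility precedes allocation. This also stands: a misread cut-off would affect both arms alike.
- **The slip may exist only in the article.** Sites would be expected to screen from the full protocol and their own forms, which are not shown. That is fair. It makes the check on site documents a query and not a finding about conduct, but the printed figure is still wrong.
- **The diagnosis and remedy could be narrower.** A dropped zero would also explain the row, since 100 mg/mL is 100 g/L, or 10 g/dL. The document cannot decide between the two explanations, although g/dL is the customary unit. Either way the intended cut-off is 10 g/dL. Likewise, 6 mmol/L is an acceptable rounding of 6.2, so changing the molar figure is a refinement and not needed to fix the error.

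**Conclusion.** The concern holds. One exclusion limit is printed as two values about 9.7-fold apart (1.0 against 9.7 g/dL, or 0.62 against 6 mmol/L). The mass conversion rests on no assumption. The molar conversion rests on the monomer mass, and the conclusion is the same anywhere in the range tried. The intended cut-off is almost certainly 10 g/dL, with mg/mL most likely printed for g/dL.

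The consequence is small. The molar limb remains usable and shows the intent, and there is no effect on the sample size, the allocation, the analysis or the validity of the dose comparison. Whether any site applied the wrong figure cannot be judged from the article. This is a correction worth making, not a threat to the trial.

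**What to change.** Change the row in Table 1 to: Anemia (hemoglobin < 10 g/dL, i.e. 6.2 mmol/L). The change of mass unit is essential. Giving 6.2 in place of 6 is advisable, because otherwise a patient between 9.67 and 10.0 g/dL is excluded by one figure and not by the other. The sponsor should confirm that 6.2 matches the intended limit.

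The sponsor should also check that the full protocol and any eligibility form used at the sites state the threshold in g/dL.

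The cost is a one-line correction and a document check, with no change to the design, sample size or analysis.

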### Intervention and comparator descriptions

Eligible patients are randomly assigned in a 1:2 fashion to either the usual dose group (valsartan 80 mg/day) or the high dose group (valsartan up to 320 mg/day). In the usual dose group, valsartan 40 mg twice a day is administrated throughout the study period. For those in the high dose group, dose is up-titrated to 80 mg twice a day before hospital discharge and finally to 160 mg twice a day after 2 weeks during outpatient visits. The process of the trial conduct is illustrated in Figure 2. If up-titration is not clinically feasible, either because of hypotension or deepening azotemia, the previous dose is administered subsequently as maximal tolerable dose.

**Figure 2 F2:**
[figure not shown]
**Titration scheme of study drug**. In the usual dose group, valsartan 40 mg twice a day is administrated throughout the study period. For those in the high dose group, dose is up-titrated to 80 mg twice a day before hospital discharge and finally to 160 mg twice a day after 2 weeks during outpatient visits.

### Outcomes measurement

The primary outcome of the study is the changes of the echocardiographic indices of LV remodeling, which is the LV volume index at end-systolic and end-diastolic time as measured by modified Simpson's rule [25], during the study period. Echocardiographic records from participating institute are sent to the core echocardiography laboratory for the analysis. Secondary outcomes include occurrence of predefined clinical events (all-cause death, cardiovascular death, hospitalization, revascularization), changes of plasma level of neurohormone (B-type natriuretic peptide, norepinephrine, aldosterone), and echocardiographic indices other than ventricular volume (ejection fraction, wall motion score index, mitral inflow, tissue Doppler index) at 12 months (Table 2). Neurohormone measurement will be conducted in a core laboratory.

**Table 2 T2:** Study Objectives

Primary Objective	Secondary objectives
Change in the LV index measured by echocardiography from baseline to follow-up	Change in functional capacity (NYHA class)

	All cause mortality

	Cardiovascular death

	Hospitalization

	Revascularization procedures (emergency and elective)

	Change in B-type natriuretic peptide (BNP) level

	Change in plasma norepinephrine level

	Change in serum aldosterone level

	Change in ejection fraction

	Change in MI index (wall motion score index)

	Change in sphericity index

	Change in mitral inflow index (mitral E/A ratio, mitral deceleration time)

	Change in tissue Doppler index (mitral Ea)

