### Statistical analyses

A consultant group of statisticians has been appointed to conduct the statistical work for this study, including data completion, interim analysis, application of statistical technique and final assessment. The principal analysis will be an intention-to-treatment basis. For baseline characteristics, continuous variables are assessed using the Student *t *test and discrete variables are compared using the chi-square test. The two-sided null-hypothesis for the primary outcome measure states that usual and high dose valsartan lead to the same expected change of ventricular remodeling during the 12 months after MI. This null-hypothesis will be tested by application of an analysis of covariance that adjusts for age, gender, and cardiovascular risk factors. Primary outcome will be compared using 2-sample *t *tests. Event-free cumulative survival rates are plotted using the Kaplan-Meier method and comparisons are made between patients with and those without clinical events using the log-rank test. A Cox proportional hazards model with the use of forward selection based on the likelihood ratio test will be implemented for multivariate analysis to determine which prognostic factors identified in the univariate analysis were significantly related to 12-month clinical events. Assessments for the change of neurohormone and other echocardiographic indices will be compared between treatment groups at 12-month follow-up using 2-sample *t *tests.

We will compare proportions of missing data using chi-square tests and agreement between data collection methods using Lin's Concordance Correlation Coefficient. Additionally, sensitivity analyses will be conducted using different patient populations (per protocol population excluding patients with relevant protocol violations), different imputation techniques for missing values, and different statistical methods for taking into account covariates. A value of p < 0.05 will be considered statistically significant.

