## Conclusions

The enrollment criteria for the VALID is different from those of other major post-MI ACE inhibitor trials in that patients with milder systolic LV dysfunction (EF <50%) is eligible for VALID while more severe form of LV dysfunction (EF <35% or clinical sign of heart failure) was required for enrollment in previous major clinical trials [9-12]. Two factors have been considered when deciding the cut-off value for LV dysfunction. First, the majority of patients referred to the participating hospital receive reperfusion therapy in Korea [28], leading to substantial increment of the number of the patients with more preserved LV contractile function. Second, as the proportion of elderly population among the patients with acute MI is increasing, the pattern of post-MI remodeling may exhibit a different picture. Elderly patients seem to undergo LV remodeling more commonly than younger patients, even after smaller size acute MI. In the PREAMI study [29], ACE inhibitor (8 mg/day of perindopril) could reduce progressive LV remodeling in elderly patients who had a relatively preserved LV function with EF ≥40%. Thus, the increasing proportion of elderly population in acute MI cases in Korea [30] can make it feasible to examine the effect of ARB agent on post-MI remodeling in the presence of moderate LV dysfunction for the VALID study.

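### Revascularizations already planned at randomisation, and admissions for them, count as secondary clinical events, diluting those comparisons to an unknown extent

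*Protocol article*

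**What the plan says.** Under Outcomes measurement, the text reads "Secondary outcomes include occurrence of predefined clinical events (all-cause death, cardiovascular death, hospitalization, revascularization"). Table 2 in the same section widens the revascularization item: "Revascularization procedures (emergency and elective"). Hospitalization is not limited by cause or by whether it was planned.

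Under Patient population, enrolment is set "within 10 days of symptom onset", and "Patients are recruited regardless of whether they received reperfusion therapy, either thrombolysis or primary percutaneous coronary intervention, or not". The one exclusion in Table 1 that touches revascularization is "Urgent need for revascularization procedure".

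Under Randomization, allocation follows the first echocardiographic estimate of ejection fraction, "which is conducted after stabilization by reperfusion therapy or conservative treatment". The Conclusions add that "the majority of patients referred to the participating hospital receive reperfusion therapy in Korea".

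Under Statistical analyses, "Event-free cumulative survival rates are plotted using the Kaplan-Meier method". The article does not say which events end event-free time.

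**The concern.** A patient who is stable after thrombolysis, who was not reperfused, or who is waiting for a staged procedure can be randomised with an elective revascularization already decided. Nothing in Table 1 keeps this patient out, and Table 2 expressly counts the procedure when it takes place. If the patient is admitted for it, the unrestricted hospitalization item counts the same decision a second time.

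That decision predates allocation, so dose cannot have influenced it. Events of this kind fall about equally in both groups and move the comparison toward no difference. In a trial that asks whether the higher dose does better, a diluted result could be misread as evidence that the usual dose is enough. Unlike low power, this shift is in the estimate itself, and a larger sample would not cure it.

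**Working it through.** **Does the rule let planned procedures in?**

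1. Elective revascularization counts (Table 2).
2. Hospitalization counts without restriction (Outcomes measurement).
3. Only urgent need is excluded (Table 1), so a non-urgent planned procedure is compatible with entry.
4. Patients stabilised by conservative treatment may be randomised (Randomization), and reperfusion is not required (Patient population).

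Together these make a procedure planned before allocation a countable event. The inclusion of elective procedures is written in words; it is not a gap left for another document.

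**What does it do to the comparison?** The article states no event rate, planned-procedure rate or power for clinical events, so there is no figure to reproduce. The following is illustration on assumptions.

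Let p be the 12-month risk of other events and q the risk of a planned procedure, equal in both groups and independent of p. The observed risk is 1 − (1 − p)(1 − q). The risk difference shrinks by the factor (1 − q), and the risk ratio moves toward 1.

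Inputs:
- Group sizes are 372 and 744 (Figure 1), with no loss to follow-up applied.
- p is assumed to be 15% in the usual-dose group.
- The relative reduction is 12%, the figure that the Background reports for death and hospitalization in the high- versus low-dose lisinopril trial. This gives 15% × 0.88 = 13.2% in the high-dose group.
- q is assumed to be 0 to 20%.
- Power uses the normal approximation with unpooled variance, two-sided 5%: Φ(difference / SE − 1.96), where SE² = a(1 − a)/372 + b(1 − b)/744 and a, b are the observed risks.

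| q | Usual dose | High dose | Risk ratio | Power |
|---|---|---|---|---|
| 0 | 15.0% | 13.2% | 0.88 | 12.5% |
| 5% | 19.3% | 17.5% | 0.91 | 10.2% |
| 10% | 23.5% | 21.9% | 0.93 | 8.8% |
| 20% | 32.0% | 30.6% | 0.95 | 7.1% |

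Example for q = 10%: 1 − 0.85 × 0.90 = 0.235; 1 − 0.868 × 0.90 = 0.2188; ratio 0.2188 / 0.235 = 0.93.

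**The same on the hazard scale.** Assume a 10% usual-dose rate of dose-modifiable events, a true hazard ratio of 0.80 on them, and planned procedures as an equal background hazard. The modifiable hazard is −ln(0.90) = 0.105 and the planned hazard is −ln(1 − q). The observed hazard ratio is (0.80 × 0.105 + planned) / (0.105 + planned). Power is from Schoenfeld's formula with one third allocated to the usual dose.

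| q | Planned share of usual-dose hazard | Observed hazard ratio | Power |
|---|---|---|---|
| 0 | 0% | 0.80 | 18% |
| 2% | 16% | 0.83 | 15% |
| 5% | 33% | 0.87 | 13% |
| 10% | 50% | 0.90 | 10% |
| 20% | 68% | 0.94 | 8% |

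Both calculations give the same direction. In both, power is low before any dilution, so the practical harm is mainly in the estimate.

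**The case against.** All-cause hospitalization and any revascularization are recognised endpoints, and they avoid having to judge in an open-label trial whether a procedure was planned. The article calls its clinical events predefined, and operational definitions may stand in a full protocol or case report form that is not shown. These are secondary outcomes, and Sample size already says that the study is likely to be underpowered for them. The Discussion justifies the echocardiographic surrogate because dose differences in clinical outcomes are expected to be small.

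Much of this stands and limits the weight of the point. It does not remove it. Table 2 states that elective procedures count, and admitting low power does not address a shift in the estimate. The worry about open-label judgement is met by declaring planned procedures before allocation.

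Two stronger readings are tempting, and the documents do not support either:

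- **A reader might infer that planned procedures make up most of the clinical events.** No figure in the article shows this. Index reperfusion generally precedes randomisation and most patients receive it, so only staged, deferred or later elective procedures are at issue. On the hazard illustration, planned procedures pass half of the usual-dose hazard only when their rate exceeds that of the modifiable events. A steep loss of power can be shown only with a large effect: an assumed 15% versus 9% gives 80% power falling to 66, 54 and 38% at 5, 10 and 20% planned procedures. That is a 40% reduction, far above the 8% and 12% reductions that the Background reports for the lisinopril dose comparison.
- **A reader might infer that a planned procedure certainly ends event-free time and hides later events.** Outcomes measurement defines no composite, and Statistical analyses does not say which events enter the Kaplan-Meier curves. As worded, its log-rank test compares patients with and without clinical events rather than the dose groups.

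**Conclusion.** The point holds as a modest but real weakness in the definition of secondary events. As written, revascularizations already planned at randomisation, and admissions for them, count although dose cannot affect them. The revascularization and hospitalization comparisons are pulled toward no difference, and so is event-free survival if it includes these events.

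The direction is clear if planned procedures are about equally common in both groups, which randomisation supports. The size cannot be determined from the article. On the assumed rates above, a risk ratio of 0.88 moves to between 0.91 and 0.95, and power falls from 12.5% to between 10.2% and 7.1%. These figures assume independence of planned and other events and no loss to follow-up; the 25% loss or missing data assumed under Sample size would lower power further.

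The primary echocardiographic outcome, the sample size of 1,116 and the separately listed death endpoints are not affected.

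**What to change.** Add a baseline field, completed before allocation, that records any planned or staged revascularization. In Outcomes measurement and Table 2, state that only revascularizations not planned at randomisation count as events, and that hospitalizations solely for such planned procedures do not count. If event-free survival includes these items, apply the same rule there, so that a planned procedure does not end event-free time. Keep all-cause counts of revascularization and hospitalization as a descriptive line.

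The declaration must come before allocation because the trial is open-label: classifying a procedure as planned afterwards could be influenced by knowledge of the dose.

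The cost is one extra baseline field, a short change of wording and fewer counted events. Treatment, dose and sample size do not change.
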